#### Additional subgroup analyses

As well as the above ITT analyses (of data from patients on the register at the time of randomisation) some further pre-planned analyses will be conducted. In particular: (1) restriction of the analyses to only those patients who remain on the register over the course of the year (unless removed due to death); (2) restriction of the analysis to those intervention practices where all staff representatives completed over 80% of the training; and (3) inclusion of those individuals subsequently added to the ‘at-risk’ register by the practice.

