### Control

Control practices produce an anonymised list of patients who meet the definition of at-risk asthma from the algorithm. They are given instructions and asked to enter a research-relevant Read code onto patients’ EHRs so that they can be identified for the purpose of data collection. However, practice staff are blind to the names and details of the patients on the list until the end of the study. The practice representatives from the control practices will also receive study newsletters for the duration of the study.

The control practices continue to provide their usual care. This may vary between practices, but reflects the recommendations of the BTS/SIGN British Asthma Guideline [7] and NICE guidelines [25]. Primary care practices in England and Wales are incentivised to provide care to BTS/SIGN standards as defined by the Quality and Outcome Framework (QOF) [27]. This recommends creating a register of all patients with asthma and offering at least annual practice-based asthma reviews (typically in nurse-led clinics). Recognised management includes checking control of asthma symptoms with the Royal College of Physicians’ three questions (RCP3Qs; i.e. difficulty sleeping, daytime symptoms, interference with usual activities), checking smoking status and offering cessation advice, assessing/teaching inhaler technique, assessing and offering advice on adherence, and delivering patient self-management education which may include provision of action plans and self-monitoring tools [28]. Follow-up in secondary care outpatient clinics and use of emergency primary and care services is available as usual for patients, if required.

After completion of the trial, control practice staff will be permitted to undertake the eLearning training and un-blind and modify the register in the same way as intervention practices could at the beginning of the study.

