### Sample size

A total sample size of 8204 patients from 235 practices will provide 90% power to detect a difference in the primary outcome (asthma crisis events) from 7% to 5% (effect size of 0.3) assuming a cluster size of 35 and intraclass correlation coefficient (ICC) of 0.01. These estimates are from the event rate and prevalence of predicted hospitalisations and A&E attendance, as a whole and per practice, obtained from a database of 48,000 patients obtained from Optimum Patient Care, and the cluster size and ICC from our regional trial [22]. The average cluster size was estimated from CRNs. Patients will, as noted above, only be removed from the register in exceptional circumstances and we estimate that less than 10% of patients will leave their practice [31]. Therefore, we planned to evaluate a total of approximately 9170 patients with at-risk asthma from 262 practices. However, the initial average cluster size (39 patients per cluster) was greater than estimated and we propose to increase the sample size to 270 practices with 10,530 patients. If more than 10% of practices do not undergo minimum training and flagging, additional practices will be recruited. A decision to stop the study will be considered if the power of the study is reduced to less than 80% or when more than 30% of practices fail to undergo training to a minimal degree and/or do not activate the flag.

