#### Health economic analyses

In line with the primary analysis, the health economic base-case analysis will be conducted on an ITT basis. Appropriate unit costs [32] will be assigned to each item of resource use for a standard price year. The incremental cost of the at-risk register compared with standard NHS care without an at-risk register, over the 12-month trial period, will then be estimated by comparing the mean overall cost (to the NHS) in each arm of the study (with adjustment for other factors, e.g. clustering). Similarly, the incremental effect will be estimated by comparing the mean number of asthma crisis events between arms. Additionally, based on data from other sources, we will attempt to assign an estimated loss in quality of life to each asthma-related crisis event, in order to enable the incremental effect to also be estimated in terms of Quality-adjusted Life Years (QALYs).

The incremental cost and incremental effect will subsequently be used to estimate the cost-effectiveness of the at-risk register. If dominance occurs, where the at-risk register is both associated with a lower (higher) cost and is more (less) effective, then the at-risk register would be estimated to be cost-effective (or not). Alternatively, the incremental cost-effectiveness ratio (ICER) [33] will be estimated by dividing the incremental cost by the incremental effect, where this will be compared to any relevant thresholds, e.g. [34] in order to assess value for money.

Non-parametric bootstrapping will be used to explore the level of uncertainty surrounding the cost-effectiveness results, and to construct cost-effectiveness acceptability curves [35]. Sensitivity analysis [33] will also be undertaken to assess the robustness of conclusions to changes in key assumptions, including the aforementioned additional analyses.

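### Two of the three additional analyses select practices or patients after randomisation in the intervention arm only, so their between-arm comparisons are not protected by randomisation

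*Protocol article*

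**What the plan says.** The section on additional subgroup analyses in the protocol article pre-plans three analyses beyond the intention-to-treat analysis:

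- (1) "restriction of the analyses to only those patients who remain on the register over the course of the year", with an exception for removal because of death;
- (2) "restriction of the analysis to those intervention practices where all staff representatives completed over 80% of the training";
- (3) "inclusion of those individuals subsequently added to the" at-risk register by the practice.

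The Intervention section gives the power to delete patients (exceptionally, with documented justification) and to add patients to the intervention practices, throughout the study. In the control arm, "practice staff are blind to the names and details of the patients on the list until the end of the study" (Control section). The same section opens the eLearning and register editing to control practices only after the trial is complete.

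The sections on individual patients, the intervention and the effectiveness analyses tie the primary analysis to the original register, by intention to treat. The economic base case is also by intention to treat, but its sensitivity analysis covers changes in key assumptions, "including the aforementioned additional analyses".

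**The concern.** Analyses (2) and (3) are defined by what staff do after allocation, and only intervention staff can do it. The section gives no matching rule for control practices.

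- **Analysis (2).** Practices in which every representative finished more than 80% of the training are self-selected for engagement. Engagement may well go with better asthma care and a lower event rate whatever the intervention does. On the natural reading, they are set against all control practices.
- **Analysis (3).** Staff add patients whom they judge to be at risk. Additions are allowed all year and follow-up runs for 12 months from flag activation. A patient could therefore be added because of a crisis event inside the window, and nothing in the section stops that event from counting.
- **Analysis (1).** Deletion by staff choice is also one-sided. The exception for death deals with one outcome-related removal and no other.

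Such comparisons can show benefit or harm from selection alone. They carry pre-planned status, and the economic section uses them to test how robust its conclusions are. The Sample size section allows for practices that fail to train or to activate the flag, so an estimate of the effect under adequate implementation will be wanted.

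**Working it through.** **The plan's own figure.** The Sample size section states: "A total sample size of 8204 patients from 235 practices will provide 90% power". Its inputs are event rates of 7% and 5%, 35 patients per practice and an ICC of 0.01. The article gives no alpha; two-sided 0.05 is assumed here.

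- Per arm, uncorrected: [1.96·√(2×0.06×0.94) + 1.2816·√(0.07×0.93 + 0.05×0.95)]² / 0.02² = 2,962.
- With continuity correction: 3,061.
- Design effect: 1 + 34×0.01 = 1.34.
- Total: 2 × 3,061 × 1.34 = 8,203.5, or 8,204; divided by 35 this is 234.4, or 235 practices.

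The stated size is reproduced and is not in dispute. It supplies the 7% event rate, the ICC and the planned 2-point difference.

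**Set-up for the illustrations.** The true effect is nil, with a 7% rate in both arms. From the Sample size and Randomisation sections: 270 practices at 1:1 gives 135 per arm, with 39 patients per practice and 10% loss (the article says less than 10%). Control patients: 135×39×0.9 = 4,738.5. Remaining cluster size: 35.1. Design effect: 1 + 34.1×0.01 = 1.341. Effective control n: 4,738.5/1.341 ≈ 3,534. All selection parameters below are assumptions, because the article gives none.

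**Analysis (2).** Let a share s of intervention practices qualify, with an underlying rate r times that of the rest. The rate in the rest is 0.07/(s·r + 1 − s), and the rate in qualifying practices is r times that. Effective n in the restricted arm is 3,534·s. Worked case, s = 0.5 and r = 0.8:

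- rest: 0.07/0.9 = 7.78%; qualifying: 6.22%;
- SE = √(0.07×0.93/3,534 + 0.0622×0.9378/1,767) = 0.0072;
- shift = 0.0078/0.0072, or 1.08 SE before rounding; P(|Z| > 1.96) ≈ 19%.

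| s | r | Restricted arm | OR against 7% | Chance of p < 0.05 |
|---|---|---|---|---|
| 0.3 | 0.7 | 5.38% | 0.76 | 51% |
| 0.3 | 0.9 | 6.49% | 0.92 | 9% |
| 0.5 | 0.8 | 6.22% | 0.88 | 19% |
| 0.7 | 0.7 | 6.20% | 0.88 | 23% |
| 0.7 | 0.9 | 6.77% | 0.97 | 6% |

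**Analysis (3).** Add a fraction a of extra patients with event rate p: rate = (0.07 + a·p)/(1 + a).

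- a = 0.05, p = 0.10: 0.075/1.05 = 7.14%, OR 1.02.
- a = 0.20, p = 0.20: 0.11/1.20 = 9.17%, OR 1.34.

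**Analysis (1).** Remove a fraction q with event rate p: rate = (0.07 − q·p)/(1 − q).

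- Low-risk deletions, q = 0.02 to 0.10 and p = 0 to 0.03: 7.08% to 7.78%, against the intervention.
- High-risk deletions, q = 0.02 to 0.10 and p = 0.15: 6.84% to 6.11%, in its favour.

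**The case against.** The strongest reply is that these analyses are secondary. The primary analysis and the economic base case are by intention to treat, and no section gives the extra analyses any weight in the main conclusion. That stands, and it limits how serious the point is. A reader might infer that the trial's main result is compromised or that the extra analyses are meant to rescue a null result. The document supports neither, and analysis (3) would more likely count against the intervention.

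A reader might also infer that all three analyses alter the intervention arm alone. For (1) that goes too far. Patients in either arm may leave their practice (put at less than 10%) or refuse use of their data until extraction ends. Only deletion by staff choice is one-sided, and it is meant to be exceptional. The example given, palliative care, is already an exclusion in both arms.

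It can further be said that the article is condensed, names no comparator or estimator for (2), and may leave these to the analysis plan. Not naming a complier-average method is indeed no fault. But the article does fix the analysis populations, and as fixed those for (2) and (3) are asymmetric.

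Finally, register editing is part of the intervention, so describing results for the register as actually used is legitimate. That supports keeping (1) and (3) as description, not as between-arm tests.

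**Conclusion.** The concern holds for analyses (2) and (3): each selects after randomisation in the intervention arm only, and both feed the economic sensitivity analysis. It holds to a smaller degree for (1), where the bias could go either way. The primary intention-to-treat analysis is unaffected.

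The size is not known from the document. With no true effect and 30% to 70% of intervention practices qualifying at 0.7 to 0.9 times the event rate of the others, analysis (2) shows an OR of about 0.76 to 0.97 and a false-positive rate of about 6% to 51%. If better-trained practices had the higher underlying rate, the bias would reverse. With 5% to 20% more patients at a 10% to 20% event rate, analysis (3) shows about 1.02 to 1.34. The upper ends approach or exceed the planned 2-point difference.

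One scenario should not be quoted as the answer. For example, half the practices qualifying at 6% against 8% gives about 29%, which is a single point in a wide assumed range.

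**What to change.** Replace (2) with a practice-level complier-average causal effect analysis. Keep all randomised practices in both arms, use allocation as the instrument, define compliance as minimum training plus flag activation, and allow for clustering.

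The threshold of more than 80% training should not lead. The flag goes live once one member of a practice has completed both modules, so practices below that threshold are still treated. That breaks the assumption that allocation has no effect in non-complying practices, and would generally inflate the estimate. Even under the recommended definition, the assumption must be stated.

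Report (1) and (3) as descriptions of register edits within the intervention arm, or label them explicitly as non-randomised and exploratory. Do not use (1) to (3) as tests of robustness in the economic sensitivity analysis.

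The cost is a change of wording and a little more analysis. The complier-average estimate will have wider intervals than the intention-to-treat estimate and rests on the stated exclusion restriction. The primary analysis needs no change.

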#### Health economic analyses

In line with the primary analysis, the health economic base-case analysis will be conducted on an ITT basis. Appropriate unit costs [32] will be assigned to each item of resource use for a standard price year. The incremental cost of the at-risk register compared with standard NHS care without an at-risk register, over the 12-month trial period, will then be estimated by comparing the mean overall cost (to the NHS) in each arm of the study (with adjustment for other factors, e.g. clustering). Similarly, the incremental effect will be estimated by comparing the mean number of asthma crisis events between arms. Additionally, based on data from other sources, we will attempt to assign an estimated loss in quality of life to each asthma-related crisis event, in order to enable the incremental effect to also be estimated in terms of Quality-adjusted Life Years (QALYs).

The incremental cost and incremental effect will subsequently be used to estimate the cost-effectiveness of the at-risk register. If dominance occurs, where the at-risk register is both associated with a lower (higher) cost and is more (less) effective, then the at-risk register would be estimated to be cost-effective (or not). Alternatively, the incremental cost-effectiveness ratio (ICER) [33] will be estimated by dividing the incremental cost by the incremental effect, where this will be compared to any relevant thresholds, e.g. [34] in order to assess value for money.

Non-parametric bootstrapping will be used to explore the level of uncertainty surrounding the cost-effectiveness results, and to construct cost-effectiveness acceptability curves [35]. Sensitivity analysis [33] will also be undertaken to assess the robustness of conclusions to changes in key assumptions, including the aforementioned additional analyses.

#### Process evaluation analyses

A comprehensive, mixed-methods process evaluation in line with the Medical Research Council (MRC) guidance [36], a published framework on the conduct of process evaluation alongside cluster trials [37] and initial logic model of the intervention (Fig. 3) will be undertaken. Using the mixed-methods sequential explanatory approach [38], descriptive summaries of initial quantitative data will inform the focus of later qualitative research, and any novel findings from the qualitative research will generate further hypotheses for exploration with analyses of quantitative data where possible. The influence of selected moderating contextual factors (e.g. practice characteristics) on intermediary (e.g. process of care) and clinical outcomes (e.g. crisis events, asthma control) will be explored using regression models. Regression models may also be used in mediation analyses to assess potential mechanisms of the intervention.

**Fig. 3 Fig3:**
[figure not shown]
ARRISA-UK process evaluation logic model

Analyses of qualitative data from focus groups and interviews will be undertaken using Framework Analysis [39] and supported by use of NVivo 9.0 software. At least two project team members will analyse each transcript to enhance rigour. Efforts will be made to integrate qualitative and quantitative process evaluation and outcome data where possible to provide triangulation and aid interpretation of findings, e.g. using matrix approaches.

### Ethical issues and oversight

The study is being conducted in accordance with CODEX rules and guidelines for research and the Helsinki Declaration as well as the International Conference on Harmonisation (ICH) Guideline for Good Clinical Practice (GCP). The study protocol was approved by North Wales Research Ethics Committee (reference 14/WA/1211) prior to the start of the study. The study is registered on the International Standard Randomised Controlled Trials Number (ISRCTN) registry (reference ISRCTN95472706). Approval was granted by the Health Research Authority (HRA) and Confirmation of Capacity and Capability to conduct the study has been provided by primary care R&D offices (including local CRN) and/or individual practices as relevant.

Practices managers are asked to sign a contract with UEA on behalf of all practice staff. Patients will not be required to provide consent to use their data as their extracted data are anonymised. Asthma is a common condition and, therefore, patients are not potentially identifiable. All practices are asked to ensure that their patients are aware (e.g. by displaying a poster, statements on websites) that their data may be used anonymously for research as this is standard procedure in research-ready practices. The Read code identifying those patients that are at-risk remains on the practice systems and only non-identifiable data will be extracted. Quotes from patients at focus groups or interviews that are published will be anonymised. The focus group and interviews will not be exploring highly sensitive issues and, therefore, the study has no material ethical issues; however, individuals participating in the focus groups or interviews will provide written informed consent before participating.

UEA is the trial sponsor and has delegated responsibility for the overall management of the trial to the chief investigator and NCTU including the trial design, coordination, monitoring and analysis and reporting of results. The standard procedures and policies at NCTU, a UK Clinical Research Collaboration (UKCRC)-registered trial unit and the study’s Quality Management Monitoring Plan are followed. A Trial Management Group (TMG) has been set up to assist with the design, coordination and strategic management of the trial. An independent Trial Steering Committee (TSC) and independent Data Monitoring Committee (DMC) have also been set up to provide oversight on all aspects of the trial and to safeguard the interests of primary care practices and patients, including review of protocol amendments. Both the TMG and TSC have lay membership.

#### Dissemination

We will publish the results of the study in peer-reviewed journals and present the data at national and international conferences. Asthma UK, the Asthma UK Centre for Applied Research (AUKCAR) and our hospital and university media relations departments pledge to support dissemination of the study outcomes with coordinated press release and media coverage. We will use the innovative dissemination channels of the AUKCAR (websites, public lectures and blogs) and the co-applicants professional networks to ensure that findings are both disseminated and adopted into practice if the intervention is found to be effective. Asthma UK will support dissemination to patients through their network of volunteers and members, and to professionals via their Healthcare Professional Relationships Manager.

Results will be reported following the use cluster extension to the Consolidated Standards of Reporting Trials (CONSORT) and the REporting of studies Conducted using Observational Routinely collected health Data (RECORD) statements.

## Discussion

This protocol describes a study that will explore the impact of a primary care practice-wide intervention designed to improve processes of care for at-risk asthma. It is based on a previous regional study, with modifications (automatic at-risk patient identification, online training and remote anonymous data capture) which permit large-scale implementation within a UK-wide multicentre study across a large number of diverse practices.

Our intervention comprises automatic generation of a list of people with at-risk asthma using a validated algorithm based on data available from primary care EHRs that are used by more than 90% of primary care practices in the UK. This permits standardised participant identification throughout the country and also between intervention and control practices. However we permit modification of the list of at-risk patients for use by the practice as we anticipate that clinical knowledge of their patients will allow refinement of the list. In addition, patients’ at-risk status is likely to change over time. We have also automated the training aspect of the intervention so that it is delivered via an online eLearning package plus a webinar. This means that the intervention could be rolled out throughout the UK and adopted into clinical practice quickly if our intervention is deemed beneficial. In this respect, a primary-care-based intervention, which included education and asthma-nurse-led patient reviews with an emphasis on self-management plans, has previously been shown to increase in the time to first attendance with acute asthma from 126 to 194 days (HR 0.73 (0.54–1)) [40], as do interventions which utilise a practice champion [40–42]. Our intervention is encouraged by a practice champion and individuals are reminded of the training via videos sent at 6 weeks and 6 months and also every time the flag appears.

We have designed the ARRISA-UK CDSS to maximise its impact. The CDSS is a single flag which appears automatically whenever the patients’ EHRs are opened (and is, therefore, timely) and it cannot be readily switched off by practice staff (it is, therefore, inescapable). The precise nature of the flag varies somewhat between practice software (which is one of the reasons that the study is stratified for practice software) and varies from a pop-up box to one that has to be cleared before any further action can be taken. The wording of the flag is agreed by the practice representatives at the second eLearning module (the group-based session where practice-wide action plans are agreed) and can be changed during the study, if required. The flag is designed to prompt actions as agreed in the practice action plan disseminated to all staff, so allows tailoring to practices’ existing processes of care.

The data required for the primary and secondary care outcomes will be obtained from anonymous extraction of routine healthcare data, without obtaining individual informed consent as has been the case in similar studies [22, 26, 31, 43]. However, we ask all practices to inform patients that their data may be used anonymously for research and practice managers will be asked to sign a contract with UEA on behalf of all practice staff. Written informed consent will be obtained from patients to participate in focus groups or interviews. We believe that this meets ethical standards as the intervention is at practice level and it is the practice staff/infrastructure that are directly involved, not the patients. The Read code identifying patients remains on the practice systems and only non-identifiable data will be extracted. The data extraction methods meet all legal requirements (http://optimumpatientcare.org/about-us/) and using anonymous patient data in this way is a recognised strategy to improve patient care in line with the government agenda including the care.data initiative (http://www.england.nhs.uk/ourwork/tsd/care-data/).

